### Usability

The usability assessment will be performed by applying a checklist to participants who use the prototype device to perform the preemie-test. The 10 heuristics proposed by Nielsen and Marck (1994)^22^ will be adapted to build a checklist to evaluate the device, namely: (a) system visibility, (b) correspondence with the real world, (c) user control and freedom, (d) consistency of results and standardisation, (e) error prevention, (f) visual recognition rather than memorization, (g) flexibility and efficiency of use, (h) aesthetic and minimalist design, (i) help for the user to recognise, diagnose and recover from errors and (j) user documentation and help.

### Data collection

Standard operational procedures set data entries in structured questionaries. In this concurrent clinical trial, an electronic information system was developed to collect data in different hospitals, simultaneously. Entry forms validations were implemented with data values ranges to ensure the quality of the information. An audit of the data will be permanently performed and the data summary available on the project webpage. Double system, paper-based and electronic will permit audit concerning reliability and validity. Independent rater over-read all papers files and cross check with the electronic information.

### Data analysis

Demographics and baseline characteristics of the study group, as well the intervention measurements, will be summarised by the frequencies and the mean and standard deviation (SD), whereas the median and interquartile range (IQR) will be preferred for non-normally distributed continuous variables.

To model the GA prediction, computational randomisation will select two subsamples in the database. One of them to train the prediction model of GA based on skin reflectance and clinical variables, such as sex, time in an incubator, phototherapy, birth weight, among others. Another part will be for the analytical validation of the predictive model. Improvements in the existing prediction models for GA (preemie-test), will be conducted with conventional statistical and data mining analyses.

Regarding the primary endpoint, the agreement among three methods for GA will be calculated using the Intraclass coefficient correlation and Bland & Altman plots,^23^ and paired t-testing. The accuracy of the preemie-test in identifying the premature newborn, within a 1-week margin of error, will be the target of the accuracy analysis.

The relationship between the measurement of the newborn’s skin reflectance and complications due to pulmonary distress associated with immaturity will be evaluated by means of association tests and risk. The significance level for hypothesis tests will be 5%, together with 95% CIs.

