### Gestational age methods of calculation and comparators

Reference-GA (R) is calculated on enrolment, using the embryo measurement assessed by ultrasound exam at <14 weeks of gestation as a reference. Crown-rump-length (CRL) data, recorded from the ultrasound report or prenatal care book-document, will be considered the crude data, when available. Intergrowth’s 21st standard curve for ultrasound measurements from 7 weeks and 3 days up to 13 weeks and 6 days will be adjusted to all GA data, according to CRL.^18^

GA methods to calculate GA in the childbirth setting, and their comparators are as follows:Preemie-test-GA (T): data statistically determined by analysing the acquired information stored in the device’s processor.Comparators-GA (C): calculated using the first ultrasound exam after 13 weeks and 6 days of gestation and before 22 weeks (C1). When available, a second comparator is GA based on a reliable LMP (C2).^13^

We will take a scanning copy of the prenatal care book or the ultrasound report. After evaluating the data quality, the images will be discarded. To achieve a reliable LMP, we will interview the woman, as suggested by Nguyen *et al*.^13^

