### Sampling and sample size

The sample size calculation is estimated based on the primary endpoint. To test the hypothesis of equivalence between the preemie-test GA and the comparators GA, a sample of 787 subjects is necessary to detect an effect size of 10%. Using the G-Power 3.1 software,^20^ we assumed an alpha error of 0.05 and a power of test of 0.80 to support a paired t-test.

Sampling intends to arrange three groups of GA enrolment to preserve enough premature newborns with 3:2:1 proportion, similar to Wilson *et al*^21^: 392 term newborns, 263 premature newborns from 32 to 36 weeks and 6 days of GA and 132 extremely premature newborns from 24 to 31 weeks and 6 days of GA.

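### The 787 infants are exactly enough for one undivided paired analysis, with no allowance for the model-training subsample or for infants without a reliable LMP

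*Protocol article*

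**What the plan says.** Under Sampling and sample size, the calculation serves the primary endpoint, and its purpose is given as follows: "To test the hypothesis of equivalence between the preemie-test GA and the comparators GA". The resulting requirement is that "a sample of 787 subjects is necessary to detect an effect size of 10" per cent. The error rates and the test are then named: "we assumed an alpha error of 0.05 and a power of test of 0.80 to support a paired t-test". The same section allots every infant to a gestational-age stratum: "392 term newborns, 263 premature newborns from 32 to 36 weeks and 6 days of GA and 132 extremely premature newborns".

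Under Data analysis, "computational randomisation will select two subsamples in the database". Their purposes are stated: "One of them to train the prediction model of GA based on skin reflectance and clinical variables", and "Another part will be for the analytical validation of the predictive model". That paragraph closes by saying that the existing preemie-test models will be improved. The next paragraph gives the primary analyses (intraclass correlation, Bland-Altman plots, paired t-tests, preterm detection) without saying which infants they use.

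On the comparators, the Gestational age methods section says "When available, a second comparator is GA based on a reliable LMP (C2"). An ultrasound between 14 and 22 weeks is an inclusion criterion, so C1 should exist for everyone. A reliable LMP is not an inclusion criterion. Primary outcome measures names both C1 and C2 in the primary target.

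**The concern.** A sample size for a paired test counts analysed pairs. Two features of the plan reduce that count or compromise the pairs. Some infants may be used to fit the model that produces T, and some will have no C2. If neither loss is allowed for, the stated power belongs to an analysis that the plan does not provide.

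The alternative, analysing all 787 after training on part of them, keeps the number but scores T partly on infants it was fitted to. Agreement and preterm detection then look better than they would in new infants. The article places the study in the pivotal phase leading to regulatory approval, and its stated aim is to validate the test, so the reported error should come from infants the model has not seen.

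**Working it through.** **Inputs.** From Sampling and sample size: N = 787, alpha 0.05, power 0.80, paired t-test, and an effect size of 10%, read as a standardised paired difference dz = 0.10. Sidedness is not stated. The share held out for validation and the share of infants with C2 are not given, so both are assumed and shown as ranges.

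**1. Reproduce the plan's figure.** With n pairs, power = P(|T′| > t₀.₉₇₅,ₙ₋₁), where T′ is noncentral t with n−1 degrees of freedom and noncentrality dz·√n. At n = 787 the noncentrality is 0.10 × √787 = 2.805 and the power is 0.8001. This is the smallest n that reaches 0.80 two-sided. The normal approximation, ((1.960 + 0.842)/0.10)² ≈ 785, agrees. A one-sided test gives 620 and does not match. So 787 is the number of complete pairs for one two-sided test.

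**2. Look for a reserve.** 392 + 263 + 132 = 787. All infants in the strata are needed as pairs. Nothing is added for a training set or for missing C2.

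**3. T versus C2, all 787 usable for T.** Pairs = 787 × availability; enrolment needed for 787 pairs = 787 ÷ availability.

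| C2 available (assumed) | Pairs | Power at dz = 0.10 | Enrolment for 787 pairs |
|---|---|---|---|
| 90% | 708 | 0.76 | 875 |
| 80% | 630 | 0.71 | 984 |
| 60% | 472 | 0.58 | 1,312 |

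**4. T versus C1, if T comes from the model trained here and only the validation part is analysed.**

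| Held out (assumed) | Pairs | Power at dz = 0.10 | dz detectable with 80% power | Enrolment for 787 pairs |
|---|---|---|---|---|
| 80% | 630 | 0.71 | 0.11 | 984 |
| 50% | 394 | 0.51 | 0.14 | 1,574 |
| 30% | 236 | 0.33 | 0.18 | 2,624 |

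As a check on the 50% row: noncentrality 0.10 × √394 = 1.985 against a critical value of about 1.966, so power is just over one half.

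**5. Both losses together, half held out.** With C2 in 80%: 787 × 0.5 × 0.8 ≈ 315 pairs, power 0.43. With C2 in 60%: 787 × 0.5 × 0.6 ≈ 236 pairs, power 0.33.

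**6. If all 787 are analysed after training on part of them.** The number of C1 pairs is kept, but the training infants contribute in-sample differences. The direction of the error is optimistic. Its size cannot be worked out from the document.

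**The case against.** The strongest reply is that T may come from a model that already exists. The Introduction says the feasibility study supplied a prediction model and that this study aims to validate it. The Intervention section says the equipment produces a predicted gestational age and that the examiner is blinded to it, which suggests a prediction exists when the measurement is made. The split appears in a paragraph about building and improving the model, and the primary endpoint follows in a separate one. On that reading all 787 give unseen-infant values of T against C1, and the C1 problem disappears. This reading is possible, but the article does not establish it. No section freezes the earlier model or names it as the source of T, the device is described as an updated version, and Data analysis says the model will be trained and improved on this database.

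A second reply is that the split fraction and the analysis set may sit in a fuller protocol or an analysis plan. That is fair, and their absence is not the point. The point is that the article fixes N with no reserve and also fixes two uses of the data that need one.

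A third is that the percentages are assumed, and that power alone looks harsher than the change in detectable effect, which after a half split rises only from 0.10 to 0.14 SD. Both statements are true and limit the size of the claim, not its direction.

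A fourth is that C2 is only a second comparator, and the Abstract words the comparator as ultrasound or LMP. But Primary outcome measures joins C1 and C2, and the sample-size hypothesis refers to the comparators in the plural.

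**Conclusion.** The concern holds in a conditional form.

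- **T versus C2:** the stated 80% is not delivered on any reading of where T comes from, unless C2 is virtually complete. The shortfall is modest at high availability (76% power at 90%) and large at low availability (58% at 60%).
- **T versus C1:** if T comes from the model trained in this database, either power drops (71% to 33% for 80% to 30% held out) or the reported accuracy is optimistic. If T comes from a model locked before enrolment, neither applies.

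These figures rest on reading the effect size as dz = 0.10, which reproduces 787, and on assumed split and availability shares.

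A reader might infer that the C1 analysis is certainly underpowered or certainly contaminated by training data. The article does not support that, because it leaves the source of T open. A reader might also infer that a random split is invalid because siblings or infants from one centre could fall on both sides. The article says nothing about how many multiple births are expected, and the choice among internal validation schemes is a matter of judgement. Neither inference is part of this point.

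**What to change.** State which model produces the primary T, and compute that T only for infants not used to fit it. There are two direct ways:

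1. Lock a model before enrolment and apply it to all 787. Any retraining on these data is then a separate, later exercise.
2. Keep the split, and restrict the intraclass correlation, Bland-Altman, paired t-test and preterm-detection analyses to the validation subsample.

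Out-of-fold predictions for all 787 are a third option, with two caveats. The final refitted model is then never itself tested on unseen infants. Predictions within a fold also share a fitted model, so 787 of them do not simply restore the stated power.

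Whichever is chosen, restate power or precision for the number of pairs actually analysed, separately for C1 and C2, giving the split and the expected C2 availability.

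**Cost:** a change of wording and a recalculation, with no extra infants unless the sponsor wants to restore 80% power by enrolling more. The downside is that the stated power becomes less favourable and the reported error may look slightly worse.

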### Primary outcome measures

The primary target is the agreement between the GA offered by the preemie-test (T) and the GA calculated by the comparators (C1 and C2), so as to perform the new test in scenarios without the Reference-GA (R). The outcome is the difference between the GA calculated by the photobiological neonatal skin assessment methodology in relation to the age calculated by the comparators.

Another measure for the primary target is the detection of preterm newborns, considering the age before 37 weeks of pregnancy as the threshold between term and preterm births, and analysing sub-categories of preterm birth, based on GA^4^:Extremely preterm (<28 weeks).Very preterm (28–32 weeks).Moderate to late preterm (more than 32 to <37 weeks).

In this case, the outcome is the proportion of the preterm newborn correctly detected at birth, based on the photobiological test of the skin, within a 1-week error.

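### Read as worded, the primary-endpoint ICC spans three dating methods and so counts agreement between the two antenatal comparators (C1 with C2) towards the device; separate T–C1 and T–C2 ICCs should be stated

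*Protocol article*

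**What the plan says.** The protocol article, under Primary outcome measures, sets the question as device against comparator: "The primary target is the agreement between the GA offered by the preemie-test (T) and the GA calculated by the comparators (C1 and C2". It adds: "The outcome is the difference between the GA calculated by the photobiological neonatal skin assessment methodology in relation to the age calculated by the comparators". C1 against C2 is not part of either statement.

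Under Gestational age methods of calculation and comparators, C1 is the GA "calculated using the first ultrasound exam after 13 weeks and 6 days of gestation and before 22 weeks (C1". The LMP-based GA is conditional: "When available, a second comparator is GA based on a reliable LMP (C2". Neither uses the device.

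Under Data analysis, the primary endpoint is handled thus: "the agreement among three methods for GA will be calculated using the Intraclass coefficient correlation and Bland & Altman plots", followed by paired t-tests. The three methods are not named there, and the ICC is not said to be computed per pair. No null value or acceptance threshold is given for the ICC. There is only the general statement "The significance level for hypothesis tests will be 5%, together with 95% CIs".

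**The concern.** Read with the outcome definition, the three methods are T, C1 and C2. A single ICC over three columns draws on three pairs: T–C1, T–C2 and C1–C2. The last compares two antenatal datings of the same pregnancy and can be expected to be high whatever the device does. The coefficient therefore answers whether the three methods agree on average, while the stated target is whether T agrees with each comparator. The gap is widest for a weak device, which is the case a validation study most needs to recognise.

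The usual three-column ICC also needs all three values for each infant. Infants with T and C1 but no reliable LMP would drop out, although they can inform the T–C1 comparison.

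**Working it through.** **The plan's own figure.** The sample size of 787 comes from a paired t-test with effect size 0.10, alpha 0.05 and power 0.80. The normal approximation gives (1.960 + 0.842)² / 0.10² ≈ 785. The exact two-sided noncentral-t calculation gives n = 787 (power 0.8001). The figure reproduces, and the ICC question does not touch it.

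**Inputs for the ICC check**
- GA mix: 392, 263 and 132 infants (Sampling and sample size).
- Assumed: GA uniform within strata of 37–41.5, 32–37 and 24–32 weeks. The within-stratum variance is 2.43 and the between-stratum variance 16.70, so Var(GA) = 19.13 weeks² (SD about 4.4 weeks).
- Assumed: C1 error SD of 5 days (variance 0.51 weeks²) and C2 error SD of 5 or 10 days (0.51 or 2.04 weeks²), unbiased and independent. The Introduction mentions a margin of 10 days or more for second- and third-trimester ultrasound but gives no SDs.
- T is either uninformative (GA values permuted across infants) or a regression-type prediction with Var(T) = Cov(T, GA) = R² × 19.13. The R² of 0.828 is the feasibility value in the Introduction; 0.25 and 0.50 are illustrative.

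**Formula.** With equal means, the large-sample single-measure ICC is

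ICC = (mean of the pairwise covariances) / (mean of the variances).

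When the variances are similar, this is close to the mean of the pairwise ICCs.

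**Uninformative T, both comparator SDs 5 days**
- Variances: T 19.13, C1 19.64, C2 19.64. Covariances: T–C1 0, T–C2 0, C1–C2 19.13.
- T–C1 ICC = 0. C1–C2 ICC = 19.13 / 19.64 = 0.974.
- Three-method ICC = (19.13 / 3) / ((19.13 + 19.64 + 19.64) / 3) = 6.38 / 19.47 = 0.33.
- With a C2 SD of 10 days: 6.38 / 19.98 = 0.32.

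**R² 0.25, both SDs 5 days**
- Var(T) = 4.78. T–C1 ICC = 4.78 / ((4.78 + 19.64) / 2) = 0.39.
- Three-method ICC = ((4.78 + 4.78 + 19.13) / 3) / ((4.78 + 19.64 + 19.64) / 3) = 9.56 / 14.69 = 0.65.

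The same calculation for each case, with a C1 SD of 5 days and a C2 SD of 5 or 10 days:

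| Device | T–C1 | T–C2 | Three-method | Excess over mean of T–C1 and T–C2 |
|---|---|---|---|---|
| Uninformative | 0 | 0 | 0.32–0.33 | 0.32–0.33 |
| R² 0.25 | 0.39 | 0.37–0.39 | 0.63–0.65 | 0.25–0.26 |
| R² 0.50 | 0.66 | 0.62–0.66 | 0.76–0.78 | 0.12–0.13 |
| R² 0.828 | 0.89 | 0.86–0.89 | 0.90–0.92 | 0.02–0.03 |

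Simulation with the same quotas gave the same values. One-way, two-way absolute-agreement and two-way consistency ICCs behaved alike.

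**Sensitivity to comparator error.** With error SDs of 1.4 weeks (C1) and 2.0 weeks (C2), an uninformative T still gives a three-method ICC of 0.30. At R² 0.828 the three-method value is 0.846, against 0.858 for T–C1 and 0.813 for T–C2. The excess over their mean is about 0.01, and T–C1 alone is slightly higher than the three-method figure.

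**Not a wide-GA-range effect.** Within the term stratum alone (GA variance 4.5² / 12 = 1.69; both error SDs 5 days), an uninformative T gives (1.69 / 3) / ((1.69 + 2.20 + 2.20) / 3) = 0.28.

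**The case against.** The strongest reply is that the sentence does not commit to a pooled coefficient. It applies the same phrase to the ICC, Bland–Altman plots and paired t-tests. The last is pairwise by definition and the second in its standard form. The phrase may simply name the set of methods, with the pairs fixed by the outcome definition. The form of an ICC is also something an analysis plan commonly settles. The first part stands: pairwise ICCs may well be what is meant. But this is more than an omitted detail, because the wording that is given, if followed, yields a coefficient that does not measure the primary target. If the three methods were instead the Reference-GA, T and one comparator, the same problem would arise through reference–comparator agreement.

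A reader might go further and infer that a useless device would be declared validated, because the three-method ICC is significantly above zero even when T carries no information. In simulation a test of ICC = 0 did reject in every run at n = 787 and n = 394 with such a T. The documents do not support that inference. They name no test of ICC = 0 and no ICC threshold, so this rejection is not a decision rule of the trial, and a value near 0.32 would look low on its face.

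Nor does the point undermine the primary analysis as a whole. Bland–Altman plots of T against C1 would expose a useless device: with a permuted T, the limits of agreement are about ±12.2 weeks. The paired t-test would not help, since it rejected in none of 2,000 such runs because the means match. The separate analysis of preterm detection within one week is a further check.

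The loss of infants without a reliable LMP applies only to a pooled ICC. Eligibility requires an ultrasound between 14 and 22 weeks, so C1 should exist for essentially all infants, and pairwise T–C1 analyses would keep them.

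**Conclusion.** The point holds in a limited form. The stated wording for the primary-endpoint ICC does not match the stated primary target. Taken literally, it credits the device with agreement between ultrasound and LMP. The overstatement depends on C1–C2 agreement exceeding T–C agreement. With assumed comparator error SDs of 5 to 10 days it is large for a weak device (about 0.32 instead of 0; about 0.64 instead of 0.38 at R² 0.25) and small at the feasibility R² of 0.828. There it is 0.02 to 0.03 above the mean pairwise ICC, up to about 0.04 above the weaker pair, and about 0.01 with larger comparator errors.

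The sizes rest on assumed comparator errors and an assumed GA distribution within strata; the direction rests on algebra. What is affected is one of the primary agreement statistics and the set of infants it uses. The sample size, the paired differences and the Bland–Altman plots are not.

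**What to change.** In Data analysis, replace the three-method ICC wording with something like: *Absolute-agreement, single-measure ICCs with 95% CIs will be calculated separately for T versus C1 (all infants with T and C1) and for T versus C2 (infants with a reliable LMP). The C1–C2 ICC will be reported only as a benchmark, and no conclusion about the preemie-test will be drawn from a three-method ICC.*

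If pairwise ICCs were always intended, this only makes the intention explicit. It needs no new data and leaves the sample size unchanged. The cost is one sentence and a reported ICC that may be slightly lower than the three-method figure.

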Current methods of dating pregnancy remain a worldwide challenge. Early obstetric ultrasound currently offers the best due date.^7^ However, access to this type of exam is limited because of high equipment costs, poor training and skills of health professionals, or late prenatal care.^8^ Despite a 10-days or more margin of error during the second and third trimester of gestation, ultrasound is still a reasonable methodology for GA determination, when the best opportunity was lost.^7^ The calculation, based on the historical information of the last menstrual period (LMP), is impacted by the uncertainty of both the fertility days and date of conception,^9^ due to the bias of memory, the use of hormonal contraception and breastfeeding.^10^ After birth, neurological scores, such as the New Ballard,^11^ show a tendency to overestimate GA in preterm infants and underestimate GA in growth-restricted infants.^12^ Efforts to enhance the reliability of pregnancy dating, through more accurate and accessible technologies, seek to improve pregnancy outcomes and neonatal survival.^13^

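### The pooled paired t-test and ICC over the 3:2:1 quota sample are nearly blind to bias that changes with gestational age; the agreement conclusion should rest on Bland-Altman results by stratum

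*Protocol article*

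**What the plan says.** Under Primary outcome measures, "The outcome is the difference between the GA calculated by the photobiological neonatal skin assessment methodology in relation to the age calculated by the comparators". The comparators are C1 (ultrasound after 13 weeks 6 days and before 22 weeks) and, when available, C2 (reliable last menstrual period).

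Under Data analysis, "the agreement among three methods for GA will be calculated using the Intraclass coefficient correlation and Bland & Altman plots", "and paired t-testing". The three tools stand side by side. The text does not say which of them decides whether agreement has been shown.

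Under Sampling and sample size, the aim is "To test the hypothesis of equivalence between the preemie-test GA and the comparators GA", and "a sample of 787 subjects is necessary to detect an effect size of 10" per cent; "we assumed an alpha error of 0.05 and a power of test of 0.80 to support a paired t-test". The same section states: "Sampling intends to arrange three groups of GA enrolment to preserve enough premature newborns with 3:2:1 proportion". The quotas are 392 term infants, 263 at 32 to 36 weeks and 6 days, and 132 at 24 to 31 weeks and 6 days.

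Preterm sub-categories are named for the preterm-detection outcome. They are not named for the difference between the test and its comparators.

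**The concern.** The powered analysis is one mean difference over a sample that is half term and half preterm by design. A mean difference near zero then has two possible meanings: the device is unbiased throughout, or it reads too high in one half and too low in the other. The paired t-test cannot separate them. The ICC does not help, because it compares error variance with the spread of GA, and the quotas make that spread large.

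This pattern is the expected one. The article describes a prediction model trained on one random part of the database and checked on another. A least-squares type of predictor has a mean error near zero in such a split, but it pulls extreme values toward the sample mean. The most immature infants are therefore read as older than they are, and term infants as younger. The Introduction notes that existing neurological scores "show a tendency to overestimate GA in preterm infants", so the test as powered could miss, in preterm infants, a fault that the article raises against current methods.

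**Working it through.** **1. The plan's own figure.** Inputs from Sampling and sample size: effect size 10%, read as a standardised paired difference dz = 0.10; alpha 0.05; power 0.80. Exact noncentral-t power, two-sided, first reaches 0.80 at n = 787 (power 0.8001). The normal approximation, ((1.960 + 0.842)/0.10)², gives 785, and a one-sided test gives 620. So 787 is reproduced as a two-sided paired t-test. Since 392 + 263 + 132 = 787, that power needs all three quotas in one mean difference.

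**2. Cancellation.** Preterm infants number 263 + 132 = 395. With bias -b at term and +b in preterm infants:

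pooled mean = b × (395 - 392)/787 = 0.0038 b

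For b = 0.5, 1.0 and 1.5 weeks this is 0.002, 0.004 and 0.006 weeks. Rejection by the paired t-test at N = 787 stays at about 0.05, the level expected with no bias at all.

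**3. ICC and spread.** Assumption, not in the document: GA uniform within quotas (24-32, 32-37 and 37-42 weeks).

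- Mean = (392 × 39.5 + 263 × 34.5 + 132 × 28)/787 = 35.9 weeks.
- SD is about 4.5 weeks overall. Within strata it is about 1.44 (term), 1.44 (32-36 weeks) and 2.32 (24-31 weeks).

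For an unbiased test with error SD e, ICC ≈ SD²/(SD² + e²/2):

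| Assumed error SD (weeks) | Pooled | Term | 32-36 wk | 24-31 wk |
|---|---|---|---|---|
| 1.0 | 0.976 | 0.81 | 0.81 | 0.91 |
| 1.5 | 0.947 | 0.65 | 0.65 | 0.83 |
| 2.0 | 0.910 | 0.51 | 0.51 | 0.73 |

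For comparison, an assumed unselected birth mix (87-89% term, SD about 2.5-2.6 weeks) gives 0.92-0.93 at error SD 1.0 and 0.75-0.78 at error SD 2.0.

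With opposite 1-week biases added, the pooled ICC is still 0.94 (error SD 1.0) or 0.87 (error SD 2.0).

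**4. A shrunken predictor.** Take R² = 0.828 from the Introduction and assume that it holds in this sample. Expected bias at true GA g is -(1 - R²)(g - mean) = -0.172 × (g - 35.9). At the stratum means:

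- Term: -0.172 × 3.6 = -0.62 weeks
- 32-36 weeks: -0.172 × (-1.4) = +0.24 weeks
- 24-31 weeks: -0.172 × (-7.9) = +1.36 weeks

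Weighted by 392, 263 and 132, these sum to zero. The pooled ICC is 2R²/(1 + R²) = 1.656/1.828 = 0.91, while simulated stratum ICCs are 0.51, 0.53 and 0.65. The SD of the difference is √0.172 × 4.5 = 1.87 weeks, so the pooled limits are about ±3.7 weeks.

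**5. What the Bland-Altman plot would show.** Plotted against the mean of the two methods, the slope in step 4 is about -0.10 per week. Against true GA it is -0.172. The conventional plot therefore shows a trend but understates it. With ±0.5 week biases and error SD 2.0, the simulated slope was +0.02, so the trend was not visible. The pooled limits do respond: with opposite 1-week biases they widen from ±1.96 to ±2.77 weeks (error SD 1.0) and from ±3.92 to ±4.38 (error SD 2.0).

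**6. Power and precision by stratum.** At dz = 0.10 the strata alone have power 0.51 (term), 0.37 (32-36 weeks) and 0.21 (24-31 weeks). With an SD of 1.87 weeks in each, the 95% interval for the mean difference has half-width 1.96 × 1.87/√n: 0.19, 0.23 and 0.32 weeks, against 0.13 pooled.

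**The case against.** The strongest reply is that Bland-Altman plots are part of the stated analysis. A reader might infer that agreement is judged by ICC and mean difference alone; the Data analysis section does not say that. The plots would show limits of several weeks in the shrinkage example and, in most of the settings tried, a slope. This stands, and the point has to be worded around it. It does not dispose of the point. The plots are listed beside two summaries that can look excellent, and nothing says which governs. The usual horizontal axis understates the trend, and limits centred on zero do not describe a group whose centre is at +1.4 weeks.

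A second reply is that this is a condensed article, so stratified results may be in a fuller plan. A reader might infer that stratified agreement is ruled out; nothing says so. What is stated is the pooled test on which the sample size rests, and the weakness lies there.

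Third, the detection outcome already looks at preterm sub-categories within a 1-week error, so part of the harm could surface there. That also stands, but it does not stratify the primary difference.

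Fourth, the sizes are assumption-bound. The GA spread behind the feasibility R² is not given, R² depends on spread as ICC does, and the model may be revised. Stratum ICCs are lowered by range restriction and are not a fair benchmark for a device meant for the whole range. Both are right; the figures are illustrations.

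Three further inferences should not be drawn:

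- That the 50.2% preterm share (395/787) distorts predictive values. None are named, and the stated detection proportion is among preterm infants.
- That agreement between C1 and C2 materially props up a three-method ICC. In simulation it was 0.917 against 0.906.
- That the Introduction describes the term half of the pattern. Its remark on underestimation concerns growth-restricted infants, not term infants.

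**Conclusion.** The point holds in a limited form. As sized, the primary agreement test is one pooled paired t-test that has almost no power against opposite biases in term and preterm infants, and the pooled ICC is raised by the GA spread that the quotas create. The cancellation follows from the document's own counts: 0.4% of the bias remains. The larger illustration (+1.4 weeks at 24-31 weeks and -0.6 at term, with zero pooled bias and ICC 0.91) assumes uniform GA within quotas and that R² = 0.828 carries over. It also treats the comparator as free of error; comparator error would add scatter without removing the gradient. The direction does not depend on the GA distribution.

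The quotas are a sensible way to secure preterm infants; the weakness is in summarising across them. The named methods are adequate if used by stratum. This is an inexpensive improvement, not a flaw that invalidates the design.

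**What to change.** In Data analysis, state that:

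- T minus C1 and T minus C2 will each be summarised as Bland-Altman bias and limits of agreement, with 95% confidence intervals, in each of the three enrolment strata;
- each difference will also be regressed on Reference-GA, with regression-based limits. Reference-GA serves only as the horizontal axis, so the primary contrast stays test against comparators;
- the agreement conclusion rests on these results, and the pooled ICC (reported pairwise) and the pooled paired t-test are supportive only;
- stratum results are estimates with intervals, not significance tests, because the strata are not powered for dz = 0.10.

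This changes wording only: no new data, no change to the quotas and no change to the 787. The price is wider intervals per stratum (about ±0.3 weeks at 24-31 weeks under the assumptions above, and wider if only the validation part of the database is used) and a less flattering headline than a single pooled ICC.
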